**Exclusion criteria**

1.Participation in a concurrent interventional trial related to stroke or vascular disease.2.Any condition, including foreshortened life-expectancy, or severe comorbidities that would preclude treatment benefit or 12-month follow up.3.Institutionalized patients in a long-term care facility.4.Receiving maximal therapies for the inclusion comorbidity (3 maximal doses antihypertensives or maximal doses of statins.5.Computed tomography or magnetic resonance imaging shows evidence of primary intracranial hemorrhage or neoplasm.6.Active coronary artery disease.7.Severe renal disease on hemodialysis (HD) or severe hepatic dysfunction8.Decline of participation or inability to participate in our trial (Not able to follow in our center, or with cognition, mobility, or language barriers etc.).9.A severe systemic illness that will not allow for the patient to complete the 1-year trial.10.History of intolerance to statins or commonly used anti-hypertensive medications (intolerance/contraindication to statin (if elevated LDL-c is the inclusion criteria)11.Unable to tolerate antiplatelet agents.

### Randomization, allocation concealment, and blinding

2.3

An expert trial investigator will screen the patients for eligibility and consent for enrollment. Within 48 hours of screening and consenting, patients will be randomized to one of the 2 study arms. Computer-generated randomization will be performed with concealment of allocation. Random variable sized-blocks^[2–4]^ will be used to allocate patients to either of the study arms. The trial is open label; however, outcome assessors and data analysts will be blinded to the patient allocation.

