## Introduction

1

Cardiovascular disease accounts for more than 50% of deaths in the adult population, and its impact on society is immense.^[1]^ Cerebrovascular disease is a significant contributor to the problem, and its incidence is rising in the Gulf area population and around the globe. Evidence from multiple sources has shown that with aggressive risk factor management, stroke, especially recurrent stroke, is preventable.^[2]^ While there are recent studies from Qatar and the middle east on stroke subtypes, risk factors, hospital admission rates, and early prognosis, comprehensive research on the effects of prevention on disease progress or regression is urgently needed.^[3,4]^

We hypothesize that aggressive management of vascular risk factors to “recommended target levels” will lead to better vascular health. Compared to current practice, a comprehensive and coordinated approach at preventive measures will lead to more patients with better control of blood pressure (BP) and lipid levels. Improved risk factor management will result in slowing of atherosclerosis and its downstream effects, which will be measurable on sophisticated blood and imaging testing. Clinically this will translate into fewer hospital readmissions. Hence, we planned a randomized controlled trial to determine if a comprehensive and coordinated approach (led by nurses and pharmacists) at risk factor management will lead to more patients with better control of BP and lipid levels. Moreover, it will determine if better control of BP and lipid levels results in the slowing of plaque progression as measured on 3D Carotid Doppler imaging studies. Additionally, we will examine the effect of this approach on the mortality, stroke recurrence, and myocardial infarction incidence.

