### Setting and participants

2.2

This is a single-center study. All patients with a first TIA or IS would be approached for participation in the study. Patients who, in addition, also have a history of hypertension or increased low-density lipoprotein (LDL) blood levels would be enrolled from the HGH inpatient wards and the Stroke Prevention/rapid access TIA Clinic. All patients will be screened for eligibility to participate in our study based on the following criteria:

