#### Sample size

2.8.1

Based on an estimated clinically meaningful BP difference of 10% between the two study groups. We will require 200 patients in each group (alpha error set at 0.05 and beta error at 0.20, power 80%, and an estimated dropout rate of 20%).

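### If the superscript [2–4] gives the block sizes, the blocks are too small for a single-centre, open-label trial; the article should say what it means

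*Protocol article*

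**What the plan says.** Section 2.3 of the protocol article (Randomization, allocation concealment, and blinding) describes the scheme in a few sentences. On the method: "Computer-generated randomization will be performed with concealment of allocation". On blocking: "Random variable sized-blocks^[2–4]^ will be used to allocate patients to either of the study arms". On who recruits: "An expert trial investigator will screen the patients for eligibility and consent for enrollment". On timing: "Within 48 hours of screening and consenting, patients will be randomized to one of the 2 study arms". On blinding: "The trial is open label; however, outcome assessors and data analysts will be blinded to the patient allocation".

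Section 2.2 adds: "This is a single-center study". Section 2.8.1 sets 200 patients per group, so 400 allocations in equal numbers. The article mentions no stratification factor. The exclusion criteria include items that call for judgement, such as severe comorbidity that would preclude benefit and inability to take part. The inclusion criteria require willingness to return for visits.

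**The concern.** Concealment hides the next assignment from the person enrolling. It does not stop that person from inferring it from earlier assignments. In an open-label trial at one site, earlier assignments can become known to the study team, and nothing in the article says they are kept from those who recruit. The shorter the blocks, the more the past reveals about the next patient.

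A recruiter who expects a given arm could, knowingly or not, read a judgement-based criterion more or less strictly. If patients who are more motivated or easier to treat then went more often to the coordinated arm, the comparison of blood pressure and LDL, the two primary outcomes, would be biased. Blinded assessment and intention-to-treat analysis do not correct this, because the selection happens before randomisation.

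**Working it through.** **What the superscript means.** The article sets citations in the same style, for example in the Introduction: "comprehensive research on the effects of prevention on disease progress or regression is urgently needed.^[3,4". There, reference 2 supports stroke prevention and references 3 and 4 regional stroke studies. The Discussion reuses references 2 to 4 for modifiable risk factors, awareness, disability and vascular prevention. Reference 5 first appears in the Discussion, so no new methods reference enters at section 2.3. A number range directly after the words on block size is therefore more likely a range of sizes. This is an inference, and the reference list is not shown. As a size range it includes 3, which cannot split equally between two arms. The superscript needs correcting on either reading.

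**Inputs.** From the article: two equal arms, 400 allocations, one centre. Assumed: sizes 2 and 4 equally likely, one unstratified list, and a recruiter who follows every allocation in order. The article gives no predictability figure to reproduce.

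**Guessing the lagging arm.** Every block ends level, so a running tally is enough; the block boundaries need not be known. In a block of size 2b, the expected number of correct guesses (tossing a coin when level) is b + 2^(2b−1)/C(2b,b) − 1/2.

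- Size 2: 1 + 2/2 − 0.5 = 1.5
- Size 4: 2 + 8/6 − 0.5 = 2.833
- Together: (1.5 + 2.833)/6 = 0.722, or 289 of 400

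The same result by position: the tally is level at 1 point in a block of 2 and at 1 + 2/3 points in a block of 4, so at 2.667/6 = 44.4% of allocations, where the guess is right half the time. At the other 55.6% (about 222 patients) it is right (4.333 − 0.5 × 2.667)/3.333 = 90% of the time. All blocks of 2 would give 75%, and all blocks of 4 would give 70.8%, so the result depends little on the mix.

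**Certain allocations, sizes known but boundaries unseen.** Certainty arises only when a block of 4 opens with two patients in the same arm. The probability per block is 1/2 × 1/3 = 1/6, and it fixes the next two allocations. That is 2 × 1/6 = 1/3 per block; divided by the mean block length of 3 this is 1/9 = 11.1%, about 44 of 400.

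**Certain allocations, boundaries and sizes known.** The expected number per block is 2b/(b+1), so (1 + 1.333)/6 = 38.9%, about 156 of 400.

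**Alternatives.** For sizes 8, 12 and 16, correct guesses are (5.329 + 7.717 + 10.046)/36 = 64.1%, and certain allocations with known boundaries are (1.6 + 1.714 + 1.778)/36 = 14.1%.

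| Scheme | Correct guesses | Certain, boundaries known | Certain, boundaries unseen |
|---|---|---|---|
| 2 and 4 | 72.2% | 38.9% | 11.1% |
| 8, 12 and 16 | 64.1% | 14.1% | not computed |
| 8, 10 and 12 (simulated) | 65.1% | not computed | 1.2% |
| Simple randomisation | 50% | 0% | 0% |

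**The case against.** The premise is inferred: the article nowhere says in words that the blocks are of 2 to 4. The sizes are also said to vary at random, which is meant to hide the boundaries. Both points stand. They are why the finding is conditional and why 11%, not 39%, is the relevant share of certain allocations when boundaries are unseen.

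A reader might infer that concealment fails in this trial. The article does not support that. It asserts concealment, and sections 2.1 and 2.3 place screening and consent before allocation. Who holds the list, how an arm is released and whether recruiters know the sizes may be set out in the full protocol, and their absence from an article is no fault.

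A reader might also infer that the recruiting investigator sees every past allocation in order. The article does not say so. Patients come from inpatient wards and a clinic, and randomisation may fall anywhere within 48 hours of consent, which blurs the order. The figures are therefore a worst case.

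Finally, larger blocks lower the guess rate only modestly, from 72% to about 64%. That is true. Their main gain is in removing near-certainty; only simple randomisation brings the guess rate down to 50%.

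**Conclusion.** The point holds conditionally. The superscript has to be clarified in any case. If it gives block sizes, sizes of 2 and 4 are a poor choice for a single-centre, open-label trial with partly judgement-based eligibility. In the worst case about 72% of allocations can be guessed correctly and about 11% are certain; 39% would require known block boundaries. This weakens the stated concealment; it does not show that concealment has failed or that selection has occurred. The size of any resulting bias in blood pressure or LDL cannot be derived from the article.

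The figures rest on sizes 2 and 4 being equally likely and known to the recruiter, a single unstratified list, and allocations followed in order. The 72% itself needs only the running tally.

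**What to change.** State in section 2.3 whether the superscript is a citation or a size range, and correct it. If it is a size range, use one of these for all remaining allocations:

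- simple randomisation; or
- larger, randomly mixed blocks, for example 8, 12 and 16.

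Keep the sizes in the randomisation file, undisclosed to those who screen and consent. If the superscript is a citation, the actual sizes should still meet the same standard.

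The cost is a new computer-generated list and a sentence in the protocol, with slightly less exact balance. Under simple randomisation of 400, the SD of one arm's size is √(400 × 0.25) = 10 patients. A split of 180:220, two SDs from equal, keeps 4 × 180 × 220 / 400² = 99% of the efficiency of equal arms.

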### Interventions

2.4

After consent and initial evaluation and investigations, patients in the standard of care arm will have their risk factors managed according to the current protocols in place at the hospital in the prevention of recurrent stroke (Fig. 1). Whereas patients in the aggressive, coordinated management (intervention) arm will be offered a comprehensive review on mechanisms of stroke/vascular disease. Every attempt will be made to bring their risk factors to optimal control based on internationally accepted guidelines with assistance from a specially trained pharmacist and nurse practitioner. Both arms will be followed (initially every month for three months and then every three months) for one year. All stroke specialists will run the standard arm guided by HGH local protocol. Imaging studies and other tests completed at the start of the study will be repeated at the exit from the study one year following randomization. Smoking cessation programs will be offered to patients who continue to smoke, and regular exercise would be strongly encouraged. The Framingham Risk Score report cards would be discussed on each visit, which will include the status of risk factor management.

**Figure 1 F1:**
[figure not shown]
Flow diagram depicting the study procedures.

### Data collection

2.5

The study will be based in Hamad Hospital, Doha, Qatar where patients will be recruited from within the stroke program. The case record forms (CRFs) will be filled by the study investigators. If a change in a CRF is deemed necessary, a single line over what needs to be amended, to maintain it legible for reading. Then the investigator needs to countersign this addendum. CRFs will be collected be kept under lock and key. Data entries will be monitored daily, and data backed up electronically, the access to the electronic database will be limited to the PI.

### Primary outcomes

2.6

The mean difference in the BP and LDL are the study's two primary outcomes.

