**Methods/design::**

Prospective study to optimize the health of patients with TIAs and stroke admitted to the Hamad General Hospital (PROMOTE HEALTH) is an assessor-blinded, open-label, randomized, two-arm, controlled trial. Eligible patients have IS or TIA, and an additional modifiable risk factor (Hypertension or dyslipidemia) attending the stroke ward or clinic at the Weill Cornell-affiliated Hamad General Hospital. Stroke specialists will offer the control group the currently practiced best risk factor management strategies. Whereas, in the intervention arm, with the assistance of a nurse and a pharmacist, we will make aggressive attempts to meet targets of defined risk factors. The primary outcomes are the mean difference in blood pressure (BP) and low-density lipoprotein. Whereas myocardial infarction, recurrent stroke events, and mortality serve as the study's secondary outcomes. We require 200 patients per study arm to achieve a power of 80% and an alpha level of <0.05. The Medical Research Center and the Institutional Review Board have approved the study, and it was prospectively registered in a trial registry.

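### Two unranked primary outcomes, BP and LDL, share one unsplit alpha of 0.05, and the stated 80% power rests on BP alone

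*Protocol article*

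**What the plan says.** All references are to the protocol article.

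- **Outcomes.** Section 2.6 (Primary outcomes) says "The mean difference in the BP and LDL are" the trial's two primary outcomes. The abstract (Methods/design) agrees: "The primary outcomes are the mean difference in blood pressure (BP) and low-density lipoprotein". Neither place ranks the two, and neither says whether BP means systolic or diastolic.
- **Sizing.** Section 2.8.1 (Sample size) starts from one effect: "Based on an estimated clinically meaningful BP difference of 10% between the two study groups". It continues "We will require 200 patients in each group", with "alpha error set at 0.05 and beta error at 0.20, power 80" per cent and "an estimated dropout rate of 20" per cent. It gives no effect, standard deviation (SD) or power for LDL.
- **Scope of the figures.** The abstract gives 200 per arm, 80% power and alpha below 0.05 as the requirement of the study, without limiting them to BP.
- **Analysis.** Section 2.8.3 (Statistical analysis) lists a test for each type of variable. It gives no joint rule or testing order for the two primary outcomes.
- **Eligibility.** Under the inclusion criteria in section 2.2, raised systolic BP, raised LDL or a raised cholesterol ratio each suffices. Some patients can therefore enter without raised systolic BP and others without raised LDL.

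**The concern.** One alpha and one power figure describe a trial with one primary hypothesis. This trial has two, so both figures depend on the success rule: either outcome, both, or one after the other. The rule decides whether the chance of a false positive trial is 5% or nearly twice that, and whether 80% is the chance of a positive trial or only the chance of a BP result.

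The case that matters in practice is a split result, with one outcome significant and the other not. Under the article as it stands, such a result could be reported as a positive primary finding or as a failure. The abstract expects an efficacious result to have a substantial effect on stroke practice and guidelines, so the choice should be made before the results are seen.

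**Working it through.** **Inputs from the article:** two primary outcomes; alpha 0.05; power 80%; 200 per arm; dropout 20%; no interim analysis (section 2.9), so no alpha is spent elsewhere. **Assumed:** two-sided tests, since sidedness is not stated. The article gives no mean BP, SD or correlation between outcomes, so ranges are used below.

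**Step 1. The plan's own figure.** Evaluable patients: 200 × (1 − 0.20) = 160 per arm. The standardised difference detectable with 80% power is

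(1.960 + 0.842) × √(2/160) = 0.313.

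Without an SD, the 200 cannot be reproduced. If 10% is read as 14 to 16 mmHg (assumed mean 140 to 160), the implied SD is 14/0.313 ≈ 45 to 16/0.313 ≈ 51 mmHg. With an assumed SD of 15 to 30, only 14 to 73 evaluable patients per arm would be needed. The article also does not say whether 10% is relative or in percentage points. The 80% is therefore taken at face value in steps 3 and 4, with the 14 mmHg reading as a second case in step 4.

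**Step 2. Either outcome counts, each tested at 0.05.** With independent tests:

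1 − (1 − 0.05)² = 1 − 0.9025 = 0.0975.

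For bivariate normal test statistics:

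| Correlation | Family-wise error |
|---|---|
| 0 | 9.75% |
| 0.2 | 9.6% |
| 0.3 | 9.5% |
| 0.5 | 9.1% |
| 0.8 | 7.8% |

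**Step 3. Both required.** The error is at most 5%. If the tests are independent, joint power = BP power × LDL power. With BP at 80%, the result depends on an LDL power that the article does not give. Purely as illustration, an LDL power of 60%, 80% or 95% gives 0.80 × 0.60 = 48%, 0.80 × 0.80 = 64% or 0.80 × 0.95 = 76%. At correlation 0.5, the middle case rises to 68.7%. Whatever the correlation, joint power cannot exceed the smaller of the two powers.

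**Step 4. What control would cost.**

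- *Holm.* The smaller p-value is compared with 0.025. A test with exactly 80% power at 0.05 has, at 0.025, power Φ(1.960 + 0.842 − 2.241) = Φ(0.56) ≈ 71%. This is a floor for BP: when LDL passes first, BP is tested at 0.05. Guaranteeing 80% at 0.025 would need 160 × [(2.241 + 0.842)/(1.960 + 0.842)]² = 160 × 1.211 ≈ 194 evaluable, or 194/0.8 ≈ 243 randomised per arm.
- *Holm, with 10% assumed to be 14 mmHg and 160 per arm.* At SD 30, Φ(14/(30 × √(2/160)) − 2.241) = Φ(4.174 − 2.241) ≈ 97.3%. It is 99.7% at SD 25 and above 99.9% at SD 20 or less.
- *Fixed sequence, BP then LDL, each at 0.05.* The family-wise error is at most 5%, and BP power and N are unchanged.

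**The case against.** The strongest reply is that this is a condensed article, and multiplicity procedures are commonly left to an analysis plan, which is not shown. The 0.05 appears only as a sample-size input, and no section says that either outcome alone would make the trial positive. The Introduction's hypothesis speaks of BP and lipid control improving together, which fits a both-required rule at least as well. Under that rule the error is not inflated.

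Much of this stands. The absence of a detailed multiplicity procedure is not the fault. A reader might infer that the error rate does nearly double. The article does not support that, because the inflation arises only under the either-outcome reading.

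A reader might also infer that the 80% BP power is lost. That is not shown either. The fixed sequence preserves BP power in full, and on the 14 mmHg assumption it stays at 97% or more even at 0.025. Joint powers in the region of 64% need an LDL power that appears nowhere. Finally, a reader might count systolic BP, diastolic BP and LDL as three tests and quote a still higher error rate. Nothing in the article says that both pressures will be tested as primary.

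What the reply does not remove is what the article itself fixes: two equal primary outcomes, and one alpha and one power figure stated for the whole trial but derived from BP alone. A later analysis plan can add a testing rule, but the 80% in the abstract would still describe BP only.

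**Conclusion.** The point holds in limited form. The stated alpha and power do not match the stated primary outcomes until a success rule is fixed. If either outcome suffices at 0.05, the family-wise error is up to 9.75% (independent tests, two-sided), about 9.1% at correlation 0.5 and 7.8% at 0.8. If both are required, the error is at most 5%, but joint power is unknown and cannot exceed the BP power. The 9.75% rests on the either-outcome reading and on testing each outcome at the full 0.05, neither of which the article states. The 14 mmHg and the SDs are assumptions, used only to gauge the cost of the remedy. The sample size is not shown to be inadequate for BP.

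**What to change.** Before the data analysts are unblinded:

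1. Name a single BP variable for the primary outcome, for example systolic BP.
2. State the success rule and control the two tests at family-wise two-sided 0.05, by either of two equally acceptable routes:
   - **Holm:** compare the smaller p-value with 0.025 and, if it passes, the other with 0.05.
   - **Fixed sequence:** test BP at 0.05 and, only if it is significant, LDL at 0.05.
3. In the abstract and section 2.8.1, say that the 80% power applies to BP only, and add the power for LDL at the planned size, with the LDL difference and SD assumed. If Holm is chosen, report each power at 0.025.

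The text change is a few sentences. Holm lowers the first-step power of a test with exactly 80% to about 71%, though the loss is small on the 14 mmHg assumption. The fixed sequence costs BP nothing, but LDL cannot be claimed as a primary result if BP fails. If the investigators intend both outcomes to be required, no alpha adjustment is needed, but joint power must then be justified from a stated LDL effect.

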### Secondary outcomes

2.7

Recurrent events of stroke, myocardial infarction (MI), or death. Additionally, carotid plaque progression as measured on 3D Carotid Doppler imaging studies

### Statistical consideration

2.8

#### Sample size

2.8.1

Based on an estimated clinically meaningful BP difference of 10% between the two study groups. We will require 200 patients in each group (alpha error set at 0.05 and beta error at 0.20, power 80%, and an estimated dropout rate of 20%).

#### Analysis set

2.8.2

Intention to treat analysis will be utilized for all the study outcomes.

#### Statistical analysis

2.8.3

We will utilize descriptive statistics to summarize the baseline data, clinical, and laboratory characteristics of our study population. Continuous variables will be summarized using means (standard deviation) and medians (interquartile range). We will utilize the ANOVA or Mann Whitney test to compare continuous data (based on data normality). Categorical variables will be compared using the Chi-squared tests. Additionally, uni and multivariate regression will be attempted in our study. All analyses will be performed using SPSS version 22.

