**Inclusion criteria**

1.Ischemic stroke or TIA including ocular stroke such as Amaurosis Fugax, within the past year (not intracranial hemorrhage or due to trauma, malignancy or cardio-embolic related to structural heart disease)2.Meets at least one of the following three criteria:Systolic BP >140 mm Hg but <200 mm Hg average of 3 readings taken within 24 hours of admission and if based on clinic visits, then an average of three readings at least separated by 5 minutes-interval.Fasting LDL cholesterol >2.0 (measured within the previous 6 months)Total: HDL cholesterol ratio > 4.0 (measured within the previous 6 months)3.Willing to participate (by signing a consent form) and willing to return for study-related scheduled follow up visits for 1 year from the time of enrollment into the study.4.Age 18 to 90 years.

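### BP and LDL, the two primary outcomes, are compared without baseline adjustment, which gives up precision (not validity) that an ANCOVA would recover at little cost

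*Protocol article*

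**What the plan says.** Section 2.6 defines the primary outcomes in one sentence: "The mean difference in the BP and LDL are the study's two primary outcomes". It does not say whether this is the 12-month level or the change from baseline.

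Section 2.8.3 names the tests for continuous data: "We will utilize the ANOVA or Mann Whitney test to compare continuous data (based on data normality"). It then adds: "Additionally, uni and multivariate regression will be attempted in our study". No outcome, covariate or role is attached to that regression.

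Baseline information is within reach. The inclusion criteria use systolic BP (for inpatients, an "average of 3 readings taken within 24 hours of admission") and lipids ("Fasting LDL cholesterol >2.0 (measured within the previous 6 months")), although a patient needs to meet only one of three criteria. Section 2.4 says: "Imaging studies and other tests completed at the start of the study will be repeated at the exit from the study", one year after randomisation. Section 2.8.3 also plans to summarise baseline clinical and laboratory data.

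Section 2.3 describes variable-sized blocks and no stratification by BP, LDL or entry criterion.

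**The concern.** With two arms, one-way ANOVA is a t test. Neither it nor Mann-Whitney uses the patient's own starting value. Because patients qualify on BP or on lipids, a lipid-only entrant with ordinary BP can sit beside one with a systolic value close to 200 mmHg, and the reverse can happen for LDL. Baseline spread may therefore be wide, and nothing in the randomisation or the named tests takes account of it.

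Three things are at stake:

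- **Precision.** Variation in the outcome that baseline could explain stays in the error term.
- **Chance imbalance.** If the arms happen to differ at baseline, part of that difference passes into an unadjusted 12-month comparison.
- **One answer or several.** A regression that is foreseen but not specified can produce an adjusted result that competes with the unadjusted one, with no rule for which counts.

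Separately, if the normality check leads to Mann-Whitney, the test no longer estimates the mean difference that defines the outcome.

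**Working it through.** **Inputs from section 2.8.1.** 200 per arm, alpha 0.05 (taken as two-sided), power 80%, dropout 20%, and the effect: "Based on an estimated clinically meaningful BP difference of 10% between the two study groups". Evaluable per arm: 200 × 0.80 = 160.

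**Inputs assumed, because the article gives none.** Correlation r between baseline and 12-month value, 0.2 to 0.6; SD of systolic BP, 20 mmHg where a figure in mmHg is needed; control systolic BP, 140 to 160 mmHg.

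**The plan's own figure.** The 200 per arm can be neither confirmed nor refuted, since no SD, control BP or scale for the 10% is stated. With 160 evaluable, 80% power corresponds to a standardised difference of (1.960 + 0.842) × √(2/160) = 2.802 × 0.1118 = 0.313. If 10% means 14 to 16 mmHg, this implies an SD of 14/0.313 to 16/0.313, about 45 to 51 mmHg.

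**Effect of adjustment.** ANCOVA multiplies the residual variance by 1 − r². Starting from 80% unadjusted power, power becomes Φ(2.802/√(1 − r²) − 1.960). The detectable difference at SD 20 is 2.802 × 20 × √(1 − r²) × √(2/160).

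| r | variance factor | equivalent evaluable per arm (160 / factor) | power | detectable difference, SD 20 |
|---|---|---|---|---|
| 0 (unadjusted) | 1.00 | 160 | 80.0% | 6.3 mmHg |
| 0.2 | 0.96 | 167 | 81.6% | 6.1 mmHg |
| 0.4 | 0.84 | 190 | 86.4% | 5.7 mmHg |
| 0.5 | 0.75 | 213 | 89.9% | 5.4 mmHg |
| 0.6 | 0.64 | 250 | 93.8% | 5.0 mmHg |

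**If the outcome is change from baseline.** An unadjusted change score has variance factor 2(1 − r). From the same anchor its power is 60.1% at r = 0.2, 72.5% at 0.4, 80.0% at 0.5 and 87.9% at 0.6. ANCOVA does better at each value; the variance ratio of ANCOVA to change score is (1 + r)/2. With baseline in the model, the treatment coefficient is the same whether the dependent variable is the level or the change.

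**Chance imbalance.** With 200 randomised per arm and SD 20, the SE of the baseline difference is 20 × √(2/200) = 2.0 mmHg, a 95% range of ±3.9 mmHg. About r times this passes into an unadjusted 12-month comparison: 0.4 × 3.92 = 1.6 to 0.6 × 3.92 = 2.4 mmHg either way. With the 160 evaluable per arm, the SE is 20 × √(2/160) = 2.24 and the carried part is ±1.8 to ±2.6 mmHg.

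**How much power matters for BP.** If the true difference is 14 mmHg at SD 20, then 14/2.24 is more than 6 standard errors, and unadjusted power exceeds 99%.

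**The case against.** The other side has four arguments.

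1. **This is detail for an analysis plan.** Covariates are often fixed there, and regression is at least announced. That would excuse silence. But the article does name tests for continuous data, and they have no covariate. The announced regression is described as additional and as something to be attempted, so it does not become the primary model. It would still be unfair to call an adjusted analysis unplanned; it is planned but unspecified.

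2. **The unadjusted test is valid.** This stands in full. A reader might infer that omitting baseline biases the estimate or inflates type I error. Under randomisation it does neither, and the confidence interval already allows for chance imbalance over repeated trials. The loss is in efficiency, and in the estimate conditional on the imbalance that actually occurs.

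3. **The imbalance is small against the effect sought.** A reader might set ±3.9 mmHg beside 6.3 mmHg and conclude that imbalance rivals the target effect. The documents do not support that. Only about r times the imbalance carries over, and 6.3 mmHg is a detectable difference derived from an assumed SD, not the stated effect. Against 14 to 16 mmHg, the carried ±1.6 to ±2.4 mmHg is about 10 to 17%; against 6.3 mmHg it is 25 to 38%.

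4. **Baseline may predict weakly.** Entry BP may be taken within a day of admission and entry LDL may be six months old, so r could be near the low end, where the gain is 4% of variance. Section 2.4 does not name BP or LDL among the repeated tests, and no patient needs to qualify on both. This limits the size of the gain; it does not favour the unadjusted test.

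If the outcome is change from baseline, baseline already enters the comparison and cannot be called ignored. The change score is still less efficient than ANCOVA over the range examined.

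**Conclusion.** The point holds as a recommendation about efficiency and clarity. The article fixes tests without a baseline covariate for its two primary outcomes and leaves the regression without content. One of the two named tests does not estimate the stated outcome.

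The size depends on a correlation that the article does not give. Over 0.2 to 0.6 the variance falls by 4 to 36%, and 80% power becomes about 82 to 94%. For BP the practical gain may be slight if the 10% is a relative difference of about 14 to 16 mmHg, because power would then be ample at an SD of 20. No such margin can be claimed for LDL, since section 2.8.1 sizes the trial on BP alone. The result of an unadjusted analysis would remain valid, only less precise than it could be.

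**What to change.** - In section 2.8.3, name as the primary analysis of BP and of LDL, separately, an ANCOVA of the 12-month value on arm, with the baseline value of the same variable as covariate. Report the adjusted mean difference with its 95% CI.
- In section 2.6, say whether the mean difference refers to the 12-month level or to change. The ANCOVA treatment estimate is the same for both, but the wording should be settled.
- Keep the unadjusted ANOVA or Mann-Whitney comparison as supportive.
- Do not base treatment-effect claims on the unspecified regression.
- Use the same model for carotid plaque, with baseline plaque as covariate.

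The cost is analysis wording, with no added patients or visits, provided that baseline BP and LDL are recorded for every patient and not only for the criterion on which the patient qualified. The article should confirm this.
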